### Inclusion and exclusion criteria

The inclusion criteria for the study are as follows:

The woman with ovarian cancer is a patient at one of the participating hospitals;The woman with ovarian cancer is willing and able to give informed consent for participation in the study;The woman is biologically female, aged between 18 and 99 years at the time of recruitment;The woman has been diagnosed with any stage or type (including borderline) of primary ovarian, fallopian tube or primary peritoneal cancer within the previous five years (of the date of completing the survey); andThe woman has already been informed of their diagnosis of ovarian cancer at a previous appointment and the administrator is confident the woman with ovarian cancer understands what they have been told. If there is any doubt, the administrator must check with the clinician caring for the patient.

The participant is excluded from the study if any of the following apply:

The woman is attending the hospital or clinic to receive their diagnosis of ovarian cancer;The woman is deemed too unwell to be able to cope with the demands of filling in the survey or responding to questions;The woman is identified as being unable to cope with the demands of filling in the survey or responding to questions, or does not understand her diagnosis as a result of learning difficulties, medical conditions or mental health concerns; andThe woman has already completed the survey at a previous visit to the hospital.

### Data collection procedure

The administrator generates a unique identifier number (UIN) for the ovarian cancer patients on REDCap and some basic demographic and clinical data is entered to determine eligibility (S6 File). This information includes age at diagnosis, month and year of diagnosis, type and stage of ovarian cancer and current treatment status. This provides an overview of women attending the clinics and allows basic comparisons between the groups who do and don’t consent.

Women with ovarian cancer are then approached and taken through an informed consent process. They are given written and verbal information about the study. If they are not attending clinics directly, they can be sent this information by email or be spoken to by phone. They are taken through the purpose and outline of the study and the risks and benefits of taking part are discussed. They are informed that they do not have to participate, they do not have to answer every question, and that they can withdraw their information up to 3 months after the close of data collection. They are then asked whether or not they consent to participate in the study and if they consent, whether they wish to i) self-complete a paper survey, ii) self-complete the survey via a secure email link, iii) self-complete the survey via a secure WhatsApp link (or other online messaging app), or iv) whether they wish to have the administrator ask them the questions. Their decision is recorded. Women who receive the information in person, or by phone need to record their consent in writing, and a copy is kept in a secure location on site. In addition to the standard consent form for the study, some local sites require patients to also complete their own informed consent forms, as part of the ethics approval. One country asked for women to consent with a thumbprint. Women who receive the information by email or WhatsApp can consent electronically at the start of the survey, or they can request an administrator contact them if they have questions before deciding.

Local teams are encouraged to supply the women with some written as well as verbal information about ovarian cancer, including at least two sources of potential support and information, be they non-governmental organisations (NGO), charities, or other groups (S6 File). The process is summarised in Fig 3.

**Fig 3 pone.0298154.g003:**
[figure not shown]
Flowchart outlining the recruitment and data collection process.

### Data management

A paper log is created at each site, recording women with ovarian cancer considered for the study. It lists their name, UIN, eligibility, consent status and whether they went on to complete the survey. This is the only document that has identifiable information about participants, and the protocol requires it be kept in a locked cabinet by the LSL at the local site along with any paper copies of consent and survey answers. These records will be destroyed by the LSL six months after data collection closes. REDCap does not collect the patient’s name, nor does the paper copy of the survey have the patient’s name recorded on it.

Where surveys are completed on paper, or by interview, the administrator is responsible for entering relevant data onto REDCap using a protected login and password. This contains only non-identifiable information and is stored on the Amazon Cloud. All CLCs, LSLs and administrators involved must adhere to local or national guidelines on data privacy, as well as those included in the protocol. LSLs and administrators will only see their local site data, while the CLC can view all relevant data in their country, with the ability to download and export their non-identifiable data and see basic summary charts and statistics. The global data set is stored on REDCap system, with a protected login and password, seen only by the Principal Investigator and study team. Within REDCap, the Principal Investigator can view data at site, country and global levels. When data is downloaded for any review or analysis, the files are password protected.

The dataset for each country will be cleaned, and the data reviewed for any potential local bias or problems by the Principal Investigator and CLC. A descriptive summary report will then be produced for each country. The final dataset will then be exported from REDCAp and analysed using conventional statistical software, such as Stata or R.

### Safety considerations

This is a low-risk observational study, however, there remains a small but significant risk that participants will become uncomfortable when being questioned about their ovarian cancer experiences. Study teams are alerted to this and advised to have contact details of appropriate resources for the women. This may include referral for counselling, to a social worker, psychologist or to an NGO for support. The women will not be asked to complete the survey on the day they are given their diagnosis. Training is provided for the administrators, on administering the questionnaire, and on respectful conduct with the women.

### Data analysis

In our analysis, we seek to examine variation in key metrics (such as stage of ovarian cancer, time to diagnosis and levels of awareness) by country, region and by the socio-economic country group. In addition, we will explore associations between patient and country characteristics and key outcome measures. Table 3 gives some examples of the outcome variables and expected areas for further analysis.

**Table 3 pone.0298154.t003:** Outcome variables and expected further analysis.

Outcome variables		
• Access to chemotherapy • Access to optimal cytoreductive surgery • Access to genetic testing • Level of ovarian cancer knowledge • Time to seek help • Time from seeking help to obtaining a diagnosis • Time from diagnosis to treatment • Information needs •Impact on family finances •Priorities for action		

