### Challenges associated with ovarian cancer

Five-year survival for ovarian cancer is below 50% even in high-income countries (HICs), and there has been little progress in improving survival in recent years [9]. Nearly two-thirds of women are diagnosed with advanced disease (FIGO stage III or IV) [10]. A major screening trial using ultrasound and serial measurements of Ca 125 did not demonstrate a mortality benefit and most women are diagnosed after they develop symptoms [11]. Ovarian cancer is a difficult disease to diagnose, and patient and doctor delays are common, in part due to the non-specific nature of the symptoms [12].

At present there is little data from LMICs on the burden of ovarian cancer, including information on types of cancer and stage at diagnosis, pathways to diagnoses, clinical outcomes and the perceptions and experiences of women and their families. Even basic information in incidence is lacking. The proportion of the world’s total population covered by cancer registries included in Cancer Incidence in 5 continents volume XI is just 15%, varying by continent with just 1% of Africa, 7% of Asia and 8% of South America [13]. In addition, many LMICs have prioritised certain cancers in women such as breast and cervical cancer where screening could have a major impact on mortality [14, 15]. The lack of a clear understanding of the burden of ovarian cancer in LMICs and the subsequent lack of focus could hamper the development of approaches aimed at improving ovarian cancer outcomes.

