### Aim

In this study, we aim to establish a large patient experience evidence base, and characterise the key challenges and opportunities to improve survival and quality of life for women in LMICs. We will test our hypothesis that key factors vary by country, requiring bespoke potential health strategies. With the evidence obtained from this study we expect to raise the profile of ovarian cancer in LMICs. We hope to enable national teams to engage governments and health policy makers; secure extra funding for diagnostics, research and awareness campaigns; and improve support for women. Examples of this type of approach have been successfully undertaken in high-income countries [25–28].

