## Methods

### Design and setting

The study has been developed by the Coalition, in partnership with the International Gynecologic Cancer Society (IGCS). It is overseen by a global oversight committee (OC) comprising clinical and patient advocates from six geographic areas, together with additional data and diagnostic expertise.

This study adopts a low risk, observational, cross-sectional design. A standardised questionnaire, derived from a previously published set of questions used in an online survey with participants recruited via social media in 2018 [12], has been developed to explore the experiences of women with ovarian cancer in LMICs based on symptoms, route to diagnosis, treatment, and quality of life. This study is designed as a one-off interaction with no follow-up, with recruitment of women via participating hospital clinics to maximise uptake.

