There are several limitations to the study. First, it will only capture experiences from women who have been able to afford or access a diagnosis and subsequent treatment. In some participating countries, there is just one centre that diagnoses and treats the condition so there are many economic, geographic, societal and cultural barriers preventing symptomatic women from getting medical help. Second, the varied approach of sample selection may naturally introduce biases, but it is not feasible to apply a uniform approach in all participating sites. To account for this, sensitivity analyses will be conducted by including and excluding certain selection methods where distinct patterns are observed. Third, the minimum sample size per country will only provide a broad overview with wide confidence intervals at a standalone country level. However, the regional and global analysis will be able to determine how a country differs from the others in the study with greater accuracy, helping focus priorities for action. Finally, by running the study through known contacts of the Coalition and IGCS, there may be biases in terms of women’s experiences, particularly around levels of care, as the CLC and LSL have access to training and networks of specialist clinicians.

The results of the study with analyses at global, regional, and thematic levels, will be disseminated through peer reviewed papers, with presentations at key relevant conferences. In this way it will contribute to the knowledge base on ovarian cancer globally, and in participating LMICs. It will be supported by a media outreach campaign. Each of the CLCs will be encouraged to submit papers for publication and presentations at national and regional level in local languages to extend the reach of the study and its findings. Subject to funding, the Coalition plans to work directly with some of the country teams to develop action plans and engagement with health policy makers, which will be informed by the study findings. Some of the participating countries plan to continue data collection, subject to the appropriate permissions, and/or adapt the study for other disease areas. By publishing the protocol, survey, and findings, the authors also hope to encourage other countries to consider running the study themselves.

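### Stage at diagnosis is compared between countries only in women who survived to the survey, so advanced stage is understated by an amount that can differ by country

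*Protocol article*

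**What the plan says.** The Aim section sets the purpose: "We will test our hypothesis that key factors vary by country, requiring bespoke potential health strategies". Under Data analysis the article adds "we seek to examine variation in key metrics (such as stage of ovarian cancer, time to diagnosis and levels of awareness) by country", with region and socio-economic country group as further groupings. The tools named are chi-squared or Fisher tests for proportions and tests such as Kruskal-Wallis for continuous variables. Outlying countries are then to be identified and described.

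The sample is cross-sectional: "This study is designed as a one-off interaction with no follow-up". Eligibility is a diagnosis "within the previous five years (of the date of completing the survey". Women may also be excluded for ill health: "The woman is deemed too unwell to be able to cope with the demands of filling in the survey or responding to questions".

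Under Sample selection, one model goes back over five years of site records. The other two work from recent or forthcoming appointments, and the article says both may favour recent diagnoses. The selection method is recorded for each patient.

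The Discussion lists four limitations. The first is that "it will only capture experiences from women who have been able to afford or access a diagnosis and subsequent treatment". The others are mixed sampling, small country samples, and recruitment through known networks. The planned sensitivity analysis includes and excludes selection methods. Death before the survey is not mentioned. Table 3 lists date of diagnosis as a possible confounder for the two treatment-access outcomes only.

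**The concern.** Stage is fixed at diagnosis, but it is observed here only in women who lived long enough to be surveyed. If advanced-stage women die faster, each extra year between diagnosis and survey removes more of them than of early-stage women. The observed mix is then the stage mix of surviving patients, not of newly diagnosed ones.

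A bias equal in every country would leave the comparison roughly intact. This one need not be equal. It varies with stage-specific survival, which is likely to differ between health systems, and with the sampling window, which the sites choose. Sites within a country are encouraged to use one model, so the window can be confounded with country.

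Stage is the first key metric named. The country reports compare each country with the average and are meant for healthcare planning. A country with poor survival could be reassured about late diagnosis partly because its advanced cases had died.

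**Working it through.** **1. The plan's own precision, as a benchmark.** With n0 = 1.96² × 0.25 / e² and n = n0 / (1 + (n0 − 1)/N):
- Global: e = 0.025 gives n0 = 1536.6. With N = 823,000 (Introduction), n = 1533.7, which reproduces the stated 1534.
- Country: e = 0.10 gives n0 = 96.0. Ghana (N = 2190) gives 92.0, as stated. The minimums total 2160 over 24 countries, an average of 90.

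The planned margins are therefore ±10 points per country and ±2.5 points globally. For a difference between two countries of 90 women each, the margin is 1.96 × √(2 × 0.25/90) = ±14.6 points.

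**2. Inputs for the illustration.**
- True advanced share p = 66.7% in every country, in line with the article's background statement: "Nearly two-thirds of women are diagnosed with advanced disease (FIGO stage III or IV".
- Five-year survival S5 by stage: **assumed**, because the article says only that overall survival is below 50% even in high-income countries.
- Also assumed: constant hazards, diagnoses spread evenly over the window, and every survivor equally likely to be sampled.

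**3. Formula.** Hazard h = −ln(S5)/5. The mean proportion alive over a window of w years is m = (1 − e^(−hw))/(hw). Observed advanced share = p·m_adv / (p·m_adv + (1 − p)·m_early).

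Example, 10%/70% over five years: h = 0.461 and 0.071, so m = 0.391 and 0.841. Observed share = 0.667 × 0.391 / (0.667 × 0.391 + 0.333 × 0.841) = 48.2%.

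| Assumed S5, advanced/early | Observed, 0–5 years | Observed, 0–1 year |
|---|---|---|
| 35%/85% | 57.3% | 64.7% |
| 20%/75% | 53.4% | 63.8% |
| 10%/70% | 48.2% | 62.4% |
| 5%/60% | 44.8% | 61.3% |

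With no true difference, the spurious spread is about 12.5 points over five years and 3.4 points within one year. The first row implies overall survival of 0.667 × 35 + 0.333 × 85 = 51.7%, slightly above the article's ceiling. Without that row the five-year spread is 53.4 − 44.8 = 8.6 points.

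**4. Effect of the window alone.** At 10%/70%, a country sampled evenly over five years shows 48.2% and one sampled only in the first year shows 62.4%. That is 14.2 points apart with the same true mix and the same survival.

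**5. When true shares differ.** The country with better survival has 35%/85% and a true share of 60%, observed as 50.2%.

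| True share, worse-survival country | Observed at 10%/70% | Observed at 5%/60% |
|---|---|---|
| 65% | 46.3% | 42.9% |
| 70% | 52.0% | 48.6% |
| 75% | 58.2% | 54.9% |

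A 5-point true gap reverses. A 10-point gap nearly vanishes or reverses. A 15-point gap keeps its order but shrinks to 8.0 or 4.7 points.

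**6. Limits of the direction.** If mortality did not differ by stage, the observed share would be 66.7% and there would be no bias. If early-stage survival were also very poor (10%/25%), the observed share would be 59.1%, above the 57.3% of the best-survival row.

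**7. Numbers left within 12 months.** The share of the sample in year one is the year-one survivors divided by the five-year survivors. With p = 65%:
- 25%/80%: (0.65 × 0.873 + 0.35 × 0.978) / (5 × (0.65 × 0.541 + 0.35 × 0.896)) = 27%, about 25 of 90.
- 10%/65%: the same formula gives 32%, about 29 of 90.

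The four scenarios in step 3 give 23 to 31. With 25 to 29 women, the country margin is 1.96 × √(0.25/n), or ±18 to ±20 points.

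**The case against.** A reader might infer that the countries with the worst survival will appear to diagnose earlier. The documents do not support that as a general statement. They give no survival by stage or country, and steps 5 and 6 show that the outcome depends on the true gap and on how survival differs between stages. Nor can the inference be extended to time to diagnosis or awareness: no direction of bias for those can be derived from the article, and no claim is made.

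The plan's safeguards also deserve credit. It records the selection method for each patient, plans sensitivity analyses by method, and has each country's data reviewed for local bias. These bear directly on the window effect in step 4. Two of the three models favour recent diagnoses, which reduces loss by death, so an even five-year window is close to the worst case. The model based on forthcoming appointments may also favour women on active treatment or with complications, which could push the other way.

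On precision, a spurious gap of several points would seldom stand out between two countries when the margin is ±14.6. Finally, Table 3 is offered as examples, stage is not among its outcome variables, and detailed covariates may sit in a fuller document.

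What remains is this. The article itself states the comparison of stage, its tests, its sensitivity analysis and its limitations, and none of them deals with death before survey. Varying the selection method does not correct for survival within a method. The consent comparison covers only women identified for approach, so it cannot show those who had already died. Wide country intervals do not remove a bias, which carries more weight in the pooled regional and income-group comparisons.

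**Conclusion.** The point holds in a limited form. Provided mortality is higher in advanced disease, the stage mix among women surveyed up to five years after diagnosis understates advanced stage at diagnosis. The understatement can differ by country with survival and sampling model, so the planned comparison can mask, distort or, for small true gaps, reverse real differences.

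Under the assumed survival the understatement is about 9 to 22 points over a full five-year window (66.7% observed as 57.3% to 44.8%) and about 2 to 5 points within one year. The first range is comparable with or larger than the ±10-point country margin and well above the ±2.5-point global margin. The existence of the bias needs only stage-dependent mortality. Its size and its pattern across countries rest on assumed survival, constant hazards and even sampling, and are illustrative.

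**What to change.** - Compare stage by country, region and income group from a regression model that includes time since diagnosis. Where data allow, add a country-by-time interaction or standardise to recent diagnosis.
- Add a supportive analysis restricted to women diagnosed in the last 12 months, reported mainly by region or income group. At 90 women per country only about 25 to 29 would remain under the assumed survival, too few for a useful country estimate.
- Label the pooled five-year figure as stage among surviving patients, in the papers and the country reports.
- Add death before survey to the limitations.

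Stage and month and year of diagnosis are already recorded at eligibility screening (Data collection procedure), so no new data are needed. Screening data from women who do not consent should stay within the comparison by consent status already described there, unless approvals allow more.

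The cost is wider intervals for stage, moderate for a model using all participants and large for the 12-month restriction. Neither analysis recovers women who died before screening, so some understatement remains even within the first year.

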The site team reviews all cases on their records that have been seen in the previous five years, with a view to contacting eligible ovarian cancer patients and inviting them to participate. This approach is dependent on availability of staff resource, accessible patient records and reliable communication methods with patients. It might also catch patients who have previously stopped treatment but may also require them to attend a new appointment if they cannot be reached by email, or WhatsApp, and so completion rates may be lower;The site team reviews all cases of ovarian cancer patients who have recently attended an appointment, working backwards in a sequential manner, until they meet the minimum or preferred sample size. This requires extra resource and good record-keeping, and may mean the sample selected is skewed to those with a more recent diagnosis; andThe site team reviews all cases of ovarian cancer patients due to attend a forthcoming appointment in person or virtually, inviting eligible patients to participate at that appointment. This approach requires less staff resources, as patient notes and attendance in clinic is already factored in. It may also improve completion rates. However, this approach may result in the inclusion of a greater proportion of patients with a more recent diagnosis, those on active treatment or experiencing complications, and can add time to clinic appointments.

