**Further analysis**		
**Outcome variables**	**Predictor variables**	**Possible confounders**
Access to chemotherapy	Age on diagnosis Family income Distance to hospital Who pays for ovarian cancer care Resource level of participating site	Stage of ovarian cancer Date of diagnosis Use of neoadjuvant chemotherapy
Access to optimal cytoreductive ovarian cancer	Age on diagnosis Family income Distance to hospital Who pays for ovarian cancer care Resource level of participating site	Date of diagnosis Use of neoadjuvant chemotherapy
Levels of awareness of ovarian cancer	Education level Family income level Distance to hospital Family history	
Time to seek help for symptoms	Age Education level Family income level Who pays for ovarian cancer care First person consulted re symptoms Number of visits prior to diagnosis Level of concern over symptoms Type of symptoms Number of symptoms	

We will perform descriptive and inferential statistics, overall and by country and economic grouping using statistical softwares such as STATA and R. Categorical variables will be summarised with counts and percentages, with Chi Squared Tests or Fisher’s Exact Test used to compare proportions between groups. Continuous variables, such as time to diagnosis, will be examined graphically and summarised using appropriate metrics (mean and standard deviation or median and interquartile range depending on the distribution of the variable data). Tests, such as Kruskal-Wallis, will be applied to continuous variables. Outlying countries will be identified and described.

Appropriate regression analysis approaches will be used to examine assocations between independent and outcome variables. Binary, ordinal or nominal regression will be used depending on the nature of the outcome variable. Univariable regression will be employed to examine individual associations and multivariable regression to examine combined assocations between predictor and outcome variables.

The two free-text answers will be translated, coded and analysed using qualitative content analysis to identify categories and possible themes.

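### Access to chemotherapy, surgery and genetic testing builds up with time since diagnosis, so the unadjusted country and income-group comparisons may partly reflect how recently each sample was diagnosed

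*Protocol article*

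**What the plan says.** All references are to the protocol article.

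- **One assessment.** Design and setting: "This study is designed as a one-off interaction with no follow-up".
- **Time window.** Under Inclusion and exclusion criteria, the diagnosis must fall "within the previous five years (of the date of completing the survey"). No minimum is given. The nearest thing to one is the exclusion "The woman is attending the hospital or clinic to receive their diagnosis of ovarian cancer", and Safety considerations adds "The women will not be asked to complete the survey on the day they are given their diagnosis". A later visit is allowed, however soon it comes.
- **Outcomes.** Table 3 under Data analysis names "Access to chemotherapy • Access to optimal cytoreductive surgery • Access to genetic testing", without a time window.
- **Sampling.** Sample selection offers three models. The second (working back through recent attenders) is said to risk a skew to recent diagnoses. The third (forthcoming appointments) "may result in the inclusion of a greater proportion of patients with a more recent diagnosis", and also of women on active treatment or with complications. Study infrastructure leaves the choice to the country lead. One method per country is suggested but not required.
- **Analysis.** Data analysis compares proportions between groups by chi-squared or Fisher tests, overall and by country and economic grouping, and says outlying countries will be identified. Country reports set each country against the global or regional average.
- **Relevant data and safeguards.** Data collection procedure: "This information includes age at diagnosis, month and year of diagnosis, type and stage of ovarian cancer and current treatment status". In the Further analysis part of Table 3, the possible confounders for chemotherapy and for surgery both include "Date of diagnosis Use of neoadjuvant chemotherapy". Selection method is recorded per patient, country data are reviewed for local bias, and the Discussion promises sensitivity analyses by selection method where distinct patterns appear.

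**The concern.** Having had surgery, chemotherapy or a genetic test is a cumulative event: its probability starts near zero at diagnosis and rises to a plateau. A single cross-sectional proportion mixes that plateau, which is what access should mean, with how far along the women happen to be. If two samples differ in time since diagnosis, their proportions differ even when care is identical.

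The design makes such differences likely. The sampling models differ in recency by the article's own account, and the choice between them tends to follow country lines. The tests that pick out outlying countries and feed the country reports make no allowance for this. Those reports are intended for healthcare planning, so a difference created by the sampling route could be read as a difference in provision.

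**Working it through.** **1. The plan's own figures.** The country minimums follow the usual precision formula with finite population correction, n = n0/(1 + (n0 - 1)/N), where n0 = 1.96² × 0.25/e².

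- At e = 0.10, n0 = 96.04. For South Africa (N = 3559), n = 93.5, matching the stated 94.
- At e = 0.025 with N = 823,000, n = 1533.7, matching the stated 1534.

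Neither depends on time since diagnosis, so they neither support nor refute the point. They do give a yardstick: the country-level precision sought is ±10 points.

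**2. What the documents do not supply.** They give no waiting times to each service and no distribution of time since diagnosis under each model. What follows is an illustration, for surgery only.

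**3. Assumptions.**
- 70% of women in both countries eventually have surgery.
- Among those women, time from diagnosis to surgery is exponential with mean μ = 4 months.
- Women surveyed before surgery are counted as not having had it.
- A share r was diagnosed within the last 6 months (evenly spread) and the rest evenly over months 6 to 60.
- Country A has r = 10%, which is an even spread over 60 months. Country B has r = 50%.
- There are 94 women per country.

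**4. Formula.** Observed proportion = 0.70 × (1 - w), where w is the mean of exp(-t/μ) over the sample's time since diagnosis.

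- Months 0-6: (4/6)(1 - e^-1.5) = 0.518.
- Months 6-60: (4/54)(e^-1.5 - e^-15) = 0.0165.
- A: w = 0.1 × 0.518 + 0.9 × 0.0165 = 0.067, so observed = 0.70 × 0.933 = 65.3%.
- B: w = 0.5 × 0.518 + 0.5 × 0.0165 = 0.267, so observed = 0.70 × 0.733 = 51.3%.
- Gap = 14.0 points. SE = √(0.653 × 0.347/94 + 0.513 × 0.487/94) = 0.071, so z ≈ 2.0. The chance of p < 0.05 is about 50%, with no true difference.

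**5. Range.**

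| Share of B recent | Mean wait | Gap (points) |
|---|---|---|
| 20% | 4 months | 3.5 |
| 30% | 4 months | 7.0 |
| 50% | 3 months | 11.9 |
| 50% | 4 months | 14.0 |
| 50% | 6 months | 16.6 |
| 70% | 4 months | 21.1 |

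**6. A second, cruder model.** Suppose 80% eventual access, a fixed wait, and diagnoses spread evenly over 60 months in one country and 12 or 24 months in the other. A 3-month wait gives 76% against 70% (24 months) or 60% (12 months). A 6-month wait gives 72% against 60% or 40%. The gaps run from 6 to 32 points. If women are compared only once the wait has passed, the gap under this model is zero.

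**7. Do the planned safeguards reach the comparison?**
- *Date of diagnosis as a possible confounder.* Where collection periods overlap, it stands in well for time since diagnosis. But the two example models that list it do not list country as a predictor, so as written they do not adjust the country comparison. Genetic testing has no example row, though the article says the table gives only examples.
- *Sensitivity analysis by selection method.* It depends on patterns being noticed. Where one method serves a whole country, excluding the method drops the country rather than correcting it. It also does not equalise recency within a method.
- *Review for local bias.* Useful, but no method is attached to it.

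**The case against.** A reader might infer that women not yet treated are scored as having no access. The article does not say so. The questionnaire is in a supplementary file that is not shown, and coding rules are detail an article may leave out. A planned or not-yet answer may exist: one sample item asks about treatments still to be decided, current treatment status is recorded, and ordinal or nominal regression is allowed for. This stands, and the point does not rest on that coding. Even with a separate not-yet category, the share who have had the service still depends on recency unless the comparison is restricted, adjusted or standardised.

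A reader might also infer that countries recruiting at forthcoming appointments will look worse. For chemotherapy that does not follow. The same model is said to favour women on active treatment, which would tend to raise observed chemotherapy use, so the net direction is unknown.

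The authors also acknowledge selection-method bias and plan several safeguards. Those deserve credit but are partial, as shown in the working.

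Finally, the illustration rests on chosen inputs. A mild skew gives only a few points. Because five-year survival is below 50%, even a records-based sample will hold more recent diagnoses than an even spread implies, which narrows the contrast. Both are fair criticisms of the size, not of the mechanism.

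**Conclusion.** The point holds as a risk of confounding by recency in the stated comparisons of the three access outcomes by country and income group. It follows from what the article fixes: one survey, no minimum time since diagnosis beyond the diagnosis visit, sampling models that differ in recency and can differ by country, and unadjusted tests.

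The size cannot be derived from the documents. For surgery it is about 7-21 points when 30-70% of one sample and 10% of the other is recent, with a 4-month mean wait and 70% eventual surgery. It is smaller with a milder skew. Much of that range equals or exceeds the ±10-point country precision. For chemotherapy the direction is uncertain, and genetic testing was not modelled. The documents do not establish that any particular country will be misreported, or that women awaiting treatment are coded as lacking access.

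**What to change.** For country, region and income-group comparisons of the three access outcomes, take time since diagnosis into account using the recorded month and year of diagnosis. Either of these would do:

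1. Standardise the proportions to a common distribution of time since diagnosis, or adjust for it in a model that includes the country or group term.
2. Restrict the comparison to women beyond a minimum time since diagnosis, with the cut set before the data are examined and all women shown as a sensitivity analysis.

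In both cases, report women not yet treated separately where current treatment status identifies them, and show the distribution of time since diagnosis beside each country's access figures.

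No new data are needed. The cost is precision. Under the restriction, if half of 94 women remain, the 95% half-width at 50% goes from 1.96 × √(0.25/94) = 10.1 points to 1.96 × √(0.25/47) = 14.3 points. Standardisation keeps all women and should cost less, unless a country has very few women in some time bands.
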